#### Feasibility of recruitment and sample size

In the first stage, for the sample size required for modeling, we referred to the method of estimating sample size for multivariate logistic regression. For the categories with a smaller proportion of the outcome variables, the sample size should be at least 10 times the number of independent variables. There are two categories of dependent variables in this study (no frailty and frailty), and 20 important independent variables were initially estimated. Therefore, the sample size of the intervention group in this study is at least 200 patients. According to the literature data, the incidence of frailty in the older population with nutritional risk is approximately 26.5–54 % [18, 32, 34, 35]. Taking into account an expected incidence of 40 % and loss to follow-up of 10–20 %, we aim to include 600 patients. As for the total sample size, with reference to logistic regression modeling requirements, the modeling sample size is approximately two-thirds of the total sample size and the model verification sample size is approximately one-third of the total sample size. The total sample size is calculated to be at least 900 patients, of which at least 300 patients will be used for model verification.

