#### Statistical considerations

Descriptive results are expressed as mean and standard deviation (SD) or as number and percentage. Bivariate analyses will be performed using the χ^2^ test or Fisher’s exact test for qualitative variables and the Student *t-*test, analysis of variance (ANOVA), or Kruskal–Wallis test for quantitative variables. Logistic regression analysis will apply in variable selection and we used an entry criterion of *P* < 0.05. The data set will be divided into a training (70 %) and verification (30 %) set using random sampling. We will establish a frailty prediction model using the modeling data set, and discrimination will be expressed using area under the receiver operating curve and the Hosmer–Lemeshow test to evaluate goodness of fit [59]. As for internal validation, we will use a bootstrap technique with 1000 resamples from the training data set. The verification data set will be used for external verification, and its effectiveness evaluated according to accuracy and area under the receiver operating curve. All statistical analysis will be performed using Stata version 14 for Windows (Stata Corp, College Station, TX, USA). A *P* value of less than 0.05 will be considered statistically significant.

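### The only calibration check named for the frailty model is a Hosmer–Lemeshow test placed with the model-building data, where it cannot reveal overfitting

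*Protocol article*

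**What the plan says.** All of this stands in the protocol article, first stage, Statistical considerations, unless another section is named.

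- Model building: "We will establish a frailty prediction model using the modeling data set, and discrimination will be expressed using area under the receiver operating curve". The same sentence goes on to name "the Hosmer–Lemeshow test to evaluate goodness of fit".
- Variable selection: "Logistic regression analysis will apply in variable selection and we used an entry criterion of" P < 0.05.
- Internal validation: "we will use a bootstrap technique with 1000 resamples from the training data set". No performance measure is attached to it.
- Held-out 30%: "The verification data set will be used for external verification, and its effectiveness evaluated according to accuracy and area under the receiver operating curve".
- Significance: a general statement that a P "value of less than 0.05 will be considered statistically significant". No rule specific to the goodness-of-fit test is given.
- Sample size (Feasibility of recruitment and sample size, first stage): "20 important independent variables were initially estimated". Definition of covariates lists 29 candidates, several with three to five categories.

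The Hosmer–Lemeshow test is therefore the only calibration measure named. By its position in the text, it belongs to the data on which the model is built.

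**The concern.** A prediction model chosen from many candidates tends to give risks that are too extreme in new patients: too high at the top and too low at the bottom. The calibration slope in new data measures this; 1 is ideal and below 1 means overfitted. A useful fit check has to be able to see this fault.

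A goodness-of-fit test on the fitting data cannot. Maximum likelihood tunes the predictions to those same data, so overfitting makes the apparent agreement no worse. The verification-set measures do not fill the gap. AUC depends only on the ranking of patients, and accuracy only on which side of a cut-off they fall. Predicted risks could therefore be too extreme when the model goes into the clinic in stage 2, and none of the named measures would show it directly.

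**Working it through.** **1. The plan's own sample size.** 10 events × 20 variables = 200 events; 200 / 0.40 = 500; 500 × 1.2 = 600 for modelling; 600 / (2/3) = 900 in total; 900 − 600 = 300 for verification. The stated figures are reproduced. The article also reports 3027 enrolled (Population and inclusion and exclusion criteria, first stage). A 70/30 split of 3027 gives about 2119 and 908; of 900, it gives 630 and 270.

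**2. Why the fitting data are silent.** The likelihood equations of a logistic model with intercept are Σ(yᵢ − p̂ᵢ) = 0 and Σxᵢⱼ(yᵢ − p̂ᵢ) = 0 for every predictor j. Hence Σ(linear predictor)ᵢ(yᵢ − p̂ᵢ) = 0. Regressing y on the model's own linear predictor in the fitting data therefore returns intercept 0 and slope exactly 1, however overfitted the model is.

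**3. Pass rates without variable selection.** Simulation with 600 runs per scenario; binary predictors with 30% prevalence; five true predictors with log-odds ratio 0.5 unless marked as noise; ten risk groups; 8 df on training data and 10 df on verification data; pass means P ≥ 0.05. Sizes and the 40% incidence come from the article. The 10% incidence, effect sizes and predictor prevalence are assumptions.

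| Training / verification | Terms | Incidence | Pass, training | Pass, verification | Median slope, new data |
|---|---|---|---|---|---|
| 600 / 300 | 20 | 40% | 95.2% | 66.2% | 0.62 |
| 600 / 300 | 29 | 40% | 95.3% | 47.0% | 0.52 |
| 600 / 300 | 29, all noise | 40% | 95.3% | 18.0% | about 0 |
| 2119 / 908 | 20 | 40% | 96.7% | 86.2% | 0.84 |
| 2119 / 908 | 29 | 40% | 95.5% | 78.0% | 0.80 |
| 2119 / 908 | 29 | 10% | 95.2% | 65.2% | 0.64 |

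Over all 21 scenarios, some of them with selection at P < 0.05, the training-data pass rate was 93–98%. A pure-noise model passes as often as one with real predictors. The same test on held-out patients does react.

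**4. Pass rates among models with the fault.** Simulation with 29 binary candidates, ten of them real, selection at P < 0.05, 70% training, 300 replicates, assumed log-odds ratios 0.2–0.9. Two figures are for univariable and multivariable selection.

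| Total n | Incidence | Share with slope < 0.8 | Of these, pass on training data |
|---|---|---|---|
| 900 | 40% | 47%, 55% | 97%, 96% |
| 900 | 9% (assumed) | 89%, 89% | 97%, 96% |
| 3027 | 9% (assumed) | 30%, 36% | 89%, 95% |

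A further simulation put the pass rate among models with slope below 0.8 at 92–100%, the same as for well-calibrated models. The single 89% above is the lowest value seen.

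**5. The case of 3027 enrolled and 40% incidence.** With 29 binary candidates, ten real, univariable selection, 70% training and 300 replicates, the share with slope below 0.8 was 0.7% for log-odds ratios spread evenly over 0.2–0.9 (median slope 0.95). It was 10% for a skewed set in that range and 18% for weaker effects of 0.2–0.5. The fault is therefore much rarer here. Step 3 gives a less favourable picture at this size: with only five real predictors and all 29 terms kept, the median slope is 0.80.

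**The case against.** **Acceptance rule.** A reader might infer that the protocol takes a non-significant Hosmer–Lemeshow result as proof of fit. The article does not say so. It states that the test will be used to evaluate fit and gives a general 0.05 level for all analyses. There is no acceptance rule and no condition for moving to stage 2. This objection stands, and the point does not rest on such a rule.

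**Other safeguards.** The bootstrap and the held-out set are real protection against overfitting. In the 600-patient, 20-term scenario AUC falls from 0.67 to 0.61, and the plan would see that. It shows lost discrimination, not whether the risks are too extreme, so the objection holds only in part.

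**Condensed article.** The bootstrap measures may be specified in a fuller document, and their absence here is not in itself a fault. The article does, however, name its measures for the model-building step and for the verification set, and the calibration measure it chose cannot do the work. Only sentence order ties the test to the modelling data. If the test were also run on the verification set it would have some power, as the table in step 3 shows.

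**Size.** A reader might infer that most models built this way would be badly miscalibrated. That needs either the minimum sample, which enrolment has already passed, or an incidence near 9–10% that appears nowhere in the article. This objection largely stands.

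**Stage 2 harm.** The article gives no risk threshold for stage 2, and a slope error leaves the ranking of patients unchanged. How many patients would be misclassified cannot be derived from the document.

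**Conclusion.** The point holds in this form: the one calibration measure named is, by its position, applied to the fitting data, and there it is uninformative about overfitting. It passes about 92–100% of overfitted models, no differently from good ones. That figure is for models of correct form. A misspecified model would be rejected more often, so the test is not worthless for other faults.

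The frequency of the undetected fault is uncertain. About half or more of models have a new-patient slope below 0.8 at 900 patients and 40% incidence. About 1–18% do at 3027 and 40%, given ten real predictors and selection at P < 0.05. The share is higher with fewer real predictors and no selection, or with a much lower incidence, which is an assumption. Effect sizes are assumed throughout, and the 0.8 threshold is a working definition, not the protocol's.

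This is worth correcting before the model is used in stage 2. It does not show that the model will be miscalibrated.

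**What to change.** - Do not rest the goodness-of-fit statement on the Hosmer–Lemeshow P value.
- From the 1000 bootstrap resamples already planned, report the optimism-corrected calibration slope and intercept with 95% CI and a smoothed calibration plot. Repeat the P < 0.05 variable selection inside each resample, so that its optimism is counted.
- Report the same slope, intercept and plot in the 30% verification set, beside accuracy and AUC.
- If the corrected slope is clearly below 1, apply the bootstrap shrinkage factor to the coefficients before stage 2.
- If fit is to be called adequate, pre-specify the margin. Its value is for the sponsor to choose.

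The cost is a sentence or two in the plan and a little more analysis, with no new data. The reported fit may look less favourable than a Hosmer–Lemeshow P value alone would suggest.

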#### Definition of covariates

Potentially associated factors of frailty in the models included [16, 36–43] age, sex, ethnicity, education level, marital status, body mass index (BMI), living alone, living conditions, smoking, alcohol consumption, falling accidents in the past 12 months, immobilization for more than 4 weeks, polypharmacy, fatigue, resistance (ability to climb stairs), ambulation (ability to walk 100 m), illnesses (> 5), loss of more than 5 % body weight, nutritional risk, ADL, instrumental ADL, depression, cognitive function, handgrip strength, vision, hearing, sleeping, urinary function, and defecation function.

Age was grouped as 65–74 years old, 75–85 years old, and 85 years old and above. Ethnicity was categorized as Han and ethnic minorities. Education level was categorized as illiterate, primary school, junior high school, and high school and above. Marital status was categorized as married and divorced or widowed. Living alone was categorized as living alone or not living alone [40]. Living conditions was classified as living in a building with an elevator, a building without an elevator, or a bungalow. Polypharmacy was categorized as 0, 1–2, 3–4, 5–6, and more than 7 [16].

BMI was calculated as body weight divided by height (in meters) squared (kg/m^2^) [18] and was used to classify patients into groups of < 19 kg/m^2^, 19 to < 21 kg/m^2^, 21 to < 23 kg/m^2^, and ≥ 23 kg/m^2^. Participants’ weight in kg was measured to the nearest 0.1 kg using a digital electronic chair scale, and height (in cm) was measured to the nearest 1 mm using a stadiometer. Study participants were weighed while wearing light clothing and no shoes.

We referred to the FRAIL scale [38, 44], such as the items of fatigue, resistance (ability to climb stairs), ambulation (ability to walk 100 m), illnesses (> 5), and loss of more than 5 % body weight, which has been validated in Chinese older adults [45].

Nutritional risk was measured using the MNA-SF, a six-item scale with scores ranging from 0 to 14 points [19]. Patients were categorized into patients at risk of malnutrition (8–11 points) or malnourished (0–7 points) [39]. The MNA-SF has been validated in the Chinese population and has excellent test characteristics [10, 46].

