### Applying the frailty prediction model in the clinic

#### Population and inclusion and exclusion criteria

All older patients (age 65 years or more, BI scores ≥ 75 points, and estimated survival time > 3 months) who were hospitalized for minimum of 4 days in the wards of Peking Union Medical College Hospital, will be screened by a research assistant using the frailty prediction model. The other inclusion criteria are the same as in the first stage of the study. In the second stage, we will also exclude patients who were included in model development during the first stage.

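### The Stage 1 frailty model is selected at P < 0.05 with no described shrinkage and no calibration check in the verification set, so its predicted risks are expected to be somewhat too extreme

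*Protocol article*

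**What the plan says.** All the modelling steps stand in the first-stage section Statistical considerations.

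- Selection: "Logistic regression analysis will apply in variable selection and we used an entry criterion of" P < 0.05.
- Split: "The data set will be divided into a training (70 %) and verification (30 %) set using random sampling".
- Development measures: "discrimination will be expressed using area under the receiver operating curve and the Hosmer–Lemeshow test to evaluate goodness of fit".
- Bootstrap: "As for internal validation, we will use a bootstrap technique with 1000 resamples from the training data set".
- Verification measures: "The verification data set will be used for external verification, and its effectiveness evaluated according to accuracy and area under the receiver operating curve".

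Definition of covariates lists 29 candidate factors, introduced by "Potentially associated factors of frailty in the models included". The first-stage sample size was built on fewer: "20 important independent variables were initially estimated".

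In the second stage, patients "will be screened by a research assistant using the frailty prediction model", and the section Statistical analysis compares the model with the Fried phenotype by Kappa. The article mentions no shrinkage, penalisation or recalibration at any point. It does not say what quantity the bootstrap estimates, whether selection is repeated in each resample, or what is done with the result.

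**The concern.** Entry by significance tends to keep the variables whose estimated effects came out large in that sample. An ordinary maximum-likelihood fit of the retained variables therefore overstates them on average. In new patients, high predicted risks are then too high and low ones too low, which is a calibration slope below 1.

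The planned measures would not show this:

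- A maximum-likelihood logistic model has a calibration slope of exactly 1 in its own training data, so Hosmer–Lemeshow there cannot reveal this overfitting.
- AUC depends only on ranking, which uniform overstatement does not disturb.
- Accuracy responds only through whichever cut-off is used.
- No calibration measure is named for the verification set.

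At stake are the absolute risks that the model assigns in the clinic, and any high-risk label set at a fixed risk value.

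**Working it through.** **1. The plan's own sample size.** 10 events × 20 variables = 200 events; 200 / 0.40 = 500; 500 × 1.20 = 600 modelling patients; 600 / (2/3) = 900 in total. The stated figures reproduce. The section on the Stage 1 population gives 3027 enrolled; 0.70 × 3027 = 2119 for training.

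**2. Parameters.** With the categories in Definition of covariates, and binary coding where none is given, the first 13 factors (age to polypharmacy) need 2+1+1+3+1+3+1+2+1+1+1+1+4 = 22. The other 16 need at least 1 each. Total: at least 38.

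**3. Events per parameter at 40% incidence.**

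| Training n | Events | 20 parameters | 38 parameters |
|---|---|---|---|
| 600 | 240 | 12.0 | 6.3 |
| 2119 | 848 | 42.4 | 22.3 |

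**4. Analytic expected shrinkage.** Solve n = p / [(S − 1) ln(1 − R²/S)] for S, where R² is the Cox–Snell value. Assumption, not in the article: Nagelkerke R² 0.15 to 0.30. At 40% incidence the maximum Cox–Snell R² is 1 − exp{2[0.4 ln 0.4 + 0.6 ln 0.6]} = 0.740, so R² = 0.111 to 0.222.

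Example with p = 38 and R² = 0.111: S = 0.657 gives (−0.343) × ln(1 − 0.111/0.657) = 0.0635, and 38 / 0.0635 ≈ 600.

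| n | S, 20 parameters | S, 38 parameters |
|---|---|---|
| 600 | 0.78–0.89 | 0.66–0.80 |
| 2119 | 0.93–0.96 | 0.87–0.93 |

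**5. Simulation of the stated selection.** Set-up: 38 correlated binary candidates, 20 with true effects; forward entry at P < 0.05; calibration slope measured in 60,000 new patients; 60 training sets per row. The bootstrap columns use 12 of these sets with 30 resamples each. True AUC (0.70, 0.80) and the 10% incidence are assumptions.

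| Incidence | AUC | n | Slope in new patients | Bootstrap slope, selection repeated | Bootstrap slope, variables held fixed |
|---|---|---|---|---|---|
| 40% | 0.70 | 600 | 0.71 | 0.71 | 0.91 |
| 40% | 0.80 | 600 | 0.81 | 0.80 | 0.93 |
| 40% | 0.70 | 2119 | 0.90 | 0.89 | 0.96 |
| 40% | 0.80 | 2119 | 0.94 | 0.93 | 0.97 |
| 10% | 0.70 | 600 | 0.53 | 0.62 | 0.93 |
| 10% | 0.80 | 600 | 0.69 | 0.68 | 0.92 |
| 10% | 0.70 | 2119 | 0.78 | 0.80 | 0.95 |
| 10% | 0.80 | 2119 | 0.90 | 0.87 | 0.95 |

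Two further simulations with different settings agree at 40% incidence. One gave 0.79–0.82 at n = 540 (600 less 10% loss) and 0.95 at n = 2119. The other gave 0.74–0.81 at n = 600 and 0.91–0.94 at n = 2119.

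**6. What the correction achieves.** Applying the repeated-selection bootstrap slope cut the overstatement of risk in the top decile from about 4–8 to about 0–1 percentage points at n = 600, and from about 1–3 to about 0 points at n = 2119. A bootstrap of the fixed final model misses most of the overfitting at n = 600 and about half of it at n = 2119.

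**The case against.** The strongest reply is that this is an inference from silence in a condensed article. A reader might take it as settled that the coefficients enter the clinic unshrunk. The article does not say so, and a fuller plan could contain the step. That stands as a limit on the claim. What remains is that the steps the article does fix (selection rule, bootstrap as internal validation, accuracy and AUC for verification) neither correct nor detect the problem.

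Other stronger readings also fail:

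- A reader might suppose that the planned bootstrap already supplies the correction factor. It does so only if each resample repeats the selection and the slope is recorded. The article states neither.
- A reader might conclude that any cut-off set in Stage 1 will misclassify. One common factor with a re-estimated intercept preserves order, so a cut-off on the score or from the ROC curve picks the same patients before and after. Only a fixed absolute-risk threshold is affected, and none is stated. The Stage 2 Kappa needs some cut-off, but not necessarily one of that kind.
- The largest effects belong to the 600-patient minimum or to 10% incidence. The documented enrolment is 3027, and the article plans on 40% from a literature range of 26.5–54%. Lower incidence is plausible, because frail patients are excluded at entry and follow-up is 30 days, but it remains an assumption.
- Ridge or lasso is not an equivalent remedy. Either would replace the stated selection rule.
- A single factor does not repair bias specific to individual coefficients. This is true; it corrects calibration on average.

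**Conclusion.** The point holds as a cheap improvement to the method. P < 0.05 entry followed by an ordinary fit gave a slope below 1 in every setting examined, and the named verification measures would not expose it.

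Its size depends mainly on the number of events, which the article does not report. At 40% incidence the shrinkage needed is about 18–29% (slope 0.71–0.82) at the planned minimum of about 600 modelling patients. It is about 5–10% (slope 0.90–0.95) with 2119, which is modest. At an assumed 10% incidence and 2119 patients the slope is 0.78–0.90 in the tabulated runs.

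These figures rest on 38 parameters, a true AUC of about 0.70–0.88 across the simulations, and forward entry as the reading of the selection rule. The point concerns absolute risks and fixed-risk classification. It does not bear on ranking or AUC.

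**What to change.** Amend the first-stage Statistical considerations as follows:

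1. In each of the 1000 resamples of the training set, repeat the P < 0.05 selection and the fit, and take the calibration slope of the resulting model in the original training set.
2. Multiply the final coefficients by the mean of these slopes and re-estimate the intercept. Do this before the verification set is used and before Stage 2.
3. In the verification set, report the calibration slope and intercept alongside accuracy and AUC.
4. Report the number of events in the training set, so that the size of the correction can be judged.

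The cost is a few lines of code in a bootstrap already planned. The downside is slightly less extreme predicted risks and smaller published odds ratios. With few events the bootstrap factor may itself be too mild (0.62 against a true 0.53 in the least favourable row), which is a further reason for step 3.

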## Discussion

This project is the first to develop an early prediction model of frailty for older inpatients according to nutritional risk in a nationally representative sample of older Chinese inpatients in tertiary hospital.

In the past two decades, Fried et al. [22], Mitnitski et al. [64], Rockwood et al. [65] and other researchers [36, 66] have made great contributions to the measurement tools available for identifying frailty. These include the physical phenotype model of Fried et al. [22] and the FRAIL scale [36], the deficit accumulation models of Mitnitski [64] and Rockwood [65], which capture multimorbidity; and mixed physical and psychosocial models, such as the Tilburg Frailty Indicator [66] and Edmonton Frailty Scale [67]. However, the theoretical basis, evaluation items, evaluation methods, and applicable objects differ among these assessment tools. Additionally, none of these tools have been developed on the basis of the Asia-Pacific region, which has the largest population of older adults worldwide combined with large heterogeneity regarding population socioeconomics, provision of health care services, and ethnic diversity [58], especially among the aging Chinese population [6–8].

Many researchers have indicated that frailty is multidimensional and that its definition should comprise nutrition, cognition, mentality, ADL, and other aspects [26–30, 58]. Therefore, using this protocol, we aim to adopt findings and assessment tools from previous studies, and to develop a frailty prediction model according to nutritional risk. Early assessment to identify frailty or pre-frailty is critical in older inpatients and may help in targeting interventions to address and reduce adverse clinical outcomes and improve patient quality of life.

The limitations of this study include the older inpatients enrolled in the first stage of our study were selected from tertiary hospitals and from only one hospital in each province or municipality/city, which may limit the generalizability of our results to different settings. Additionally, the estimated sample size is not sufficiently large in the second stage of the study (*n* = 266).

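### The 30% random hold-out is labelled external but is internal split-sample validation; it cannot test transport between hospitals, and no calibration measure is planned in it

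*Protocol article*

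**What the plan says.** All of this is in the protocol article.

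- **Split** (Stage 1, Statistical considerations): "The data set will be divided into a training (70 %) and verification (30 %) set using random sampling".
- **Use of the 30%** (same section): "The verification data set will be used for external verification, and its effectiveness evaluated according to accuracy and area under the receiver operating curve".
- **Goodness of fit** (same section): the sentence on building the model in the modeling set names AUC for discrimination and "the Hosmer–Lemeshow test to evaluate goodness of fit". No such measure is listed for the verification set.
- **Internal validation** (same section): "we will use a bootstrap technique with 1000 resamples from the training data set".
- **Source of the data** (Data used for modeling; Discussion): the baseline survey of October 2018 to February 2019, in five provinces and one municipality. The limitations paragraph says patients came "from only one hospital in each province or municipality/city, which may limit the generalizability of our results". That makes six hospitals.
- **Share held out** (Stage 1, Feasibility of recruitment and sample size): "the modeling sample size is approximately two-thirds of the total sample size and the model verification sample size is approximately one-third". This differs from the 30% in Statistical considerations.
- **Stage 2** (Applying the frailty prediction model in the clinic): new patients at one hospital, restricted to a Barthel Index (BI) of at least 75. The model is compared with the Fried phenotype by Kappa.

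**The concern.** Two parts of one data set separated by random sampling differ only by chance. They share hospitals, case mix, calendar period and survey procedures. Good performance in the second part shows that the model is not badly overfitted. It says nothing about a hospital that did not contribute data, which is what a reader takes from the word *external*. The six regional sites could provide such a test, but a random split mixes them.

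The second part concerns what is measured. The model is meant to flag high-risk patients in the clinic, so its absolute risks matter. AUC depends only on ranking, and accuracy depends on the chosen cut-off and on how common frailty is. A model whose risks are systematically too high or too low at a given hospital could do well on AUC, and the planned verification would not report the error.

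**Working it through.** **1. The plan's own sample size.** The rule is "the sample size should be at least 10 times the number of independent variables", applied to the rarer outcome category, with 20 variables.
- Events: 10 × 20 = 200. At the expected 40% incidence: 200 / 0.40 = 500.
- Allowing for loss: 500 / (1 − 0.10) = 556; 500 / (1 − 1/6) = 600; 500 / (1 − 0.20) = 625. The stated 600 falls within the 10–20% range.
- Total: 600 / (2/3) = 900. Verification: 900 / 3 = 300. The plan's figures reproduce.

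**2. What the split withholds.** With 3027 patients enrolled (Stage 1, Population and inclusion and exclusion criteria):
- 70/30: 0.70 × 3027 = 2119 for fitting, 0.30 × 3027 = 908 for verification.
- Two-thirds/one-third: 2018 and 1009.

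**3. Is the training set still adequate?** At 40%, 2119 × 0.40 = 848 events. That is 848 / 20 = 42 per variable, or 848 / 29 = 29 if all 29 listed covariates are counted. Both exceed the plan's rule of 10.

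**4. Cost in precision.** The Hanley–McNeil standard error is SE = √{[A(1−A) + (n₁−1)(Q₁−A²) + (n₀−1)(Q₂−A²)] / (n₁n₀)}, with Q₁ = A/(2−A) and Q₂ = 2A²/(1+A). The AUC of A = 0.75 is an assumption; the documents give none. Then A² = 0.5625, Q₁ = 0.600, Q₂ = 0.643.
- N = 908 at 40% (n₁ = 363, n₀ = 545): SE = 0.0170, 95% half-width 1.96 × 0.0170 = 0.033.
- N = 3027 at 40% (n₁ = 1211, n₀ = 1816): SE = 0.0093, half-width 0.018.

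| Incidence | Half-width, 908 | Half-width, 3027 |
|---|---|---|
| 26.5% | 0.039 | 0.021 |
| 40% | 0.033 | 0.018 |
| 54% | 0.031 | 0.017 |

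With an assumed AUC of 0.80, the figures at 40% are 0.031 and 0.017. The ratio is about 1.8, close to √(3027/908) = 1.83.

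**5. Accuracy of a rule that calls nobody frail** is 1 − incidence: 73.5% at 26.5%, 60% at 40%, 46% at 54%. An accuracy figure therefore cannot be read without the incidence and the cut-off.

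**6. Illustration of what the split would miss.** A simulation used 200 runs, 3027 patients in six hospitals, and an assumed between-hospital standard deviation of 0.5 on the logit intercept.
- Random 70/30 split: ratio of observed to expected events 0.92 to 1.09 (95% range), mean AUC 0.75.
- Left-out hospital: ratio 0.56 to 1.56, mean AUC 0.75.

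The AUC gives no hint of the difference. The 0.5 is not from the documents, so this shows the mechanism and is not an estimate for this study.

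**The case against.** The strongest reply is that the plan already has the main safeguards. It plans a bootstrap and a goodness-of-fit test. The Discussion concedes limited generalizability. Stage 2 applies the model to new patients, excludes those used in development, and has predictive ability among its aims. Detailed calibration measures are often left to an analysis plan, and a dislike of Hosmer–Lemeshow is not an error in the document.

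Part of this stands. Choosing calibration slope over Hosmer–Lemeshow is advice, and leave-one-hospital-out is a recommendation. But the article itself fixes the label and the criteria for the verification set, so these are statements, not omissions. Stage 2 does not close the gap as written: it covers one hospital, restricts the BI range, and names Kappa against a different frailty definition, with no AUC or calibration of the model.

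A reader might also infer more than the documents support:
- *That a third of the data is discarded.* Statistical considerations says 30%, and those patients are withheld from fitting and used for testing.
- *That a random hold-out cannot show calibration.* It can, for the same population, if calibration is measured there. Only transport to another hospital is beyond it.
- *That the verification set is too small.* A 30% share of 900 is 270, below the stated minimum of 300, but 900 is itself a minimum and 3027 were enrolled, giving about 908.
- *That accuracy would be trivially near 90%.* That needs an incidence near 10%; the protocol works with 26.5–54%.

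**Conclusion.** The concern holds for the label and the missing measure. The 30% set is a random part of the same six-hospital survey, so calling it external is wrong, and no calibration measure is planned in it. These two conclusions rest on the text alone.

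The loss of precision is moderate: an interval about 1.8 times as wide, 0.033 against 0.018 at 40% incidence and an assumed AUC of 0.75. The sample remains adequate by the plan's own rule at its expected incidence. How far calibration actually differs between hospitals cannot be judged from the documents. The change should be made before the model is reported, because it determines what the authors may claim.

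**What to change.** **At minimum.** Call the random split internal validation. In the verification set, report calibration slope, calibration-in-the-large and a calibration plot beside AUC, so that accuracy and Hosmer–Lemeshow are not the only supporting measures.

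**Preferably.** Fit the model on all 3027 patients. Correct for optimism with the planned 1000 bootstrap resamples, repeating variable selection in each. Replace the random split with leave-one-hospital-out validation over the six sites. Report AUC, calibration slope and calibration-in-the-large, pooled and by site where event counts allow.

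**Stage 2.** Describe it as temporal validation at a single hospital only if AUC and calibration against the model's own outcome are added to its Statistical analysis section, and note the restriction to a BI of at least 75.

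**Separately.** Reconcile the one-third share in the sample-size section with the 30% in Statistical considerations.

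**Cost.** Revised wording and some extra computing, with no new Stage 1 data. Site-specific estimates will be imprecise, and because the article gives no per-hospital counts, the feasibility of calibration at each site has to be checked first.
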